## Methods

### Participants

To be included in the study, participants should be Hong Kong residents who (1) are fluent in Cantonese, (2) are aged between the 18 and 70 years, (3) obtained a score of 24 or higher on the Chinese version of the Social Phobia Inventory (SPIN) [37], (4) have a social anxiety disorder as assessed by the Structured Clinical Interview for disorders listed in the Diagnostic and Statistical Manual of Mental Disorders, 4th Edition [38], (5) have not received any psychological treatment at the time of registration for participation in this study, (6) have access to a computer or smartphone with an internet connection, and (7) have a valid email address. We will exclude individuals who have (1) severe depression, with a score above 30 on the Beck Depression Inventory-II (BDI-II) [39]; (2) suicidal risk in the past 3 months (score of item 9 on the BDI-II is “2” or “3” and assessed to have suicidal risk in the intake interview); and (3) a severe psychiatric condition (eg, bipolar disorder, schizophrenia, or personality disorder) diagnosed by a psychiatrist or clinical psychologist.

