### Research Design

Although deterioration in a control condition can take place [42], Steinert et al [43] conducted a meta-analysis and found only small changes in the WLC groups during short-term wait periods for clients with SAD in RCTs. Thus, this study adopts a WLC group design to conduct a 3-arm RCT as shown in Table 1.

There were 2 experimental groups that joined either the web-based or app-based iCBT program (Ease Online). The WLC group received the app-based treatment immediately after the 2 experimental groups completed the program. All 3 groups completed the same web-based questionnaire at pretest, posttest, and 3- and 6-month follow-ups. The WLC group completed the questionnaire one more time at posttest after the 2 experimental groups completed the program. To increase the submission rate of questionnaire, participants were given 2 more weeks to submit an email questionnaire after the submission deadline in the program system. The RCT was conducted in cohorts for implementation feasibility. Specifically, in each cohort, around 30 qualified participants were randomized into one of the 3 groups through computer-generated random numbers, with approximately 10 in each group. The program evaluators were blinded to the allocation of the participants. The participant recruitment flowchart is shown in Figure 1.

**Table 1 table1:** Participant group design.

Groups	Research design						
Web-based	O^a^	X^b^	O		O	O	N/A^c^
App-based	O	X	O		O	O	N/A
Waitlist control	O		O	X	O	O	O

^a^O: test.

^b^X: intervention.

^c^N/A: not applicable.

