### Outcome Measures

#### Primary Outcome Measures

The Chinese version of the SPIN [37,47] was used to assess the severity of social phobia symptoms. The measure consists of 17 items with 3 subscales: fear, avoidance, and physiological response. Participants were asked to rate their distress for each symptom during the past week on a 5-point Likert scale that ranges from “0” (not at all) to “4” (very much so). All of the item scores were summed up into a total score that ranged from 0 to 68, with a higher score indicating a higher level of anxiety. Sample items included “fear of others watching,” “avoid talking to others,” and “feeling bothered by blushing.” The α coefficient is .89 for the Chinese version of the SPIN [37].

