### Data Analysis

Intent-to-treat analysis, which is the least biased way to estimate an intervention’s effects [57], was used for data analysis. Missing data will be managed using multiple imputation [58]. Multivariate ANOVA with repeated measures will be performed to test the intervention’s effectiveness on continuous variables over time. Time (pretest, posttest, and 3- and 6-month follow-ups), condition (web-based iCBT, app-based iCBT, and WLC), and the interaction of time-by-condition will be specified as the categorical fixed factors. Medication and demographic factors (eg, gender, age, and marital status) will be specified as fixed covariates to control the potential confounding effects. Cohen *d* will be calculated as the index of the effect size both within and between groups.

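### The pretest score is a level of the time factor and not a covariate, so the posttest contrast is a change-score contrast: valid, but usually less precise than the data allow

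*Protocol article*

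**What the plan says.** The Data Analysis section names the model: "Multivariate ANOVA with repeated measures will be performed to test the intervention’s effectiveness on continuous variables over time". The categorical fixed factors are "Time (pretest, posttest, and 3- and 6-month follow-ups), condition (web-based iCBT, app-based iCBT, and WLC), and the interaction of time-by-condition". The pretest is thus one of four outcome occasions. The covariates follow: "Medication and demographic factors (eg, gender, age, and marital status) will be specified as fixed covariates". Their stated purpose is "to control the potential confounding effects". The examples in brackets illustrate demographic factors and do not bring in a symptom score. Nothing in the section holds the arms to a common pretest mean.

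The primary outcome is the SPIN total, treated as continuous: "All of the item scores were summed up into a total score that ranged from 0 to 68". Its pretest value is available in every arm, since the Research Design section reports that "All 3 groups completed the same web-based questionnaire at pretest, posttest, and 3- and 6-month follow-ups". The Participants section requires a SPIN score of at least 24 for entry.

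**The concern.** The pretest value of a symptom scale is usually the best available predictor of its later value. In this model it serves only as an outcome occasion. With a full set of time-by-condition terms, the treatment effect at posttest is the arm difference in posttest minus pretest. That amounts to adjusting for the pretest with the slope fixed at 1, whatever slope the data show.

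What is at stake is precision. The waitlist arm is treated straight after the posttest (Research Design, Table 1), so the posttest is the only comparison with an untreated control. The Limitations section says that missing data at posttest and follow-up are quite high, so information is already being lost.

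**Working it through.** **The plan's own figure.** The Sample Size section gives 3 groups, 7 measures, effect size 0.40 and α = .01, but no power. For the Pillai trace, s = min(3 − 1, 7 − 1) = 2. At N = 139:

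- df1 = 2 × 6 = 12
- df2 = 2 × (139 − 3 − 6 + 2) = 264
- λ = 139 × 2 × 0.40² = 44.48

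Power is then 0.990, and 139 is the smallest N that reaches 0.99. The figure is reproduced if 0.99 was the intended power. No stated input depends on the pretest–posttest correlation, so the point below does not change it.

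**Variance of the posttest contrast.** Let s0 and s1 be the within-arm SDs at pretest and posttest, and ρ their correlation. Per participant:

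- change score: s0² + s1² − 2ρ·s0·s1
- pretest as covariate: s1²(1 − ρ²)
- difference: s0² − 2ρ·s0·s1 + ρ²·s1² = (s0 − ρ·s1)²

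The difference is never negative. It is zero only when s0 = ρ·s1, that is, when the slope of posttest on pretest, ρ·s1/s0, equals 1.

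**Equal SDs (assumption).** The variances reduce to 2(1 − ρ) and 1 − ρ², with ratio (1 + ρ)/2. The article does not give ρ, so a range is shown. The last column is 110 per arm, the Sample Size target, times the ratio.

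| ρ | Adjusted / change variance | Excess variance of change score | Excess SE | 110 per arm analysed as change equals, if adjusted |
|---|---|---|---|---|
| 0.3 | 0.65 | 54% | 24% | 71.5 |
| 0.5 | 0.75 | 33% | 15.5% | 82.5 |
| 0.7 | 0.85 | 18% | 8.5% | 93.5 |
| 0.8 | 0.90 | 11% | 5.4% | 99 |

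At ρ = 0.5 and 110 per arm, the SE in SD units is √(1.00 × 2/110) = 0.135 for the change score and √(0.75 × 2/110) = 0.117 with adjustment. A simulation of 4,000 trials at these values gave 0.138 and 0.119, a variance ratio of 0.74.

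**Unequal SDs.** The entry threshold may make the pretest SD smaller than the posttest SD. With s0/s1 = 0.8 and ρ = 0.5, the change-score variance is 0.64 + 1 − 0.80 = 0.84 and the adjusted variance is 0.75. The ratio is 0.89, an excess of 12%.

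**The omnibus time-by-condition test.** Assume equal SDs, compound symmetry over four occasions, and an arm difference δ at posttest only. Up to a common factor, the noncentrality is:

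- planned interaction test: 0.75·δ²/(1 − ρ)
- joint test of the three later occasions, adjusted for pretest: δ²(1 + 2ρ)/[(1 − ρ)(1 + 3ρ)]
- planned/adjusted: 0.75(1 + 3ρ)/(1 + 2ρ)

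This gives 0.75 × 2.2/1.8 = 0.92 at ρ = 0.4, 0.75 × 2.5/2.0 = 0.94 at 0.5 and 0.75 × 2.8/2.2 = 0.95 at 0.6.

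**The case against.** The plan is valid and consistent with itself. The sample size was calculated for the same type of model, and the named test is the omnibus interaction, not a pairwise posttest contrast. For that test, with the effect at posttest only, the loss is about 5% to 8% of noncentrality. The correlation and the SDs are unknown, and at ρ of 0.8 or more the loss is small on any reading. All of this stands and limits the size of the point. It does not remove it: the section also plans between-group effect sizes, and reading an arm difference at posttest from this model means using the change contrast. Including the pretest in the multiple imputation would not alter the form of that contrast.

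Several stronger readings are tempting, but the documents do not support them:

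- **Bias.** Under randomisation the change-score contrast is unbiased. Only precision is lost.
- **The change score loses at every correlation below 1.** That follows only with equal SDs. In general the loss vanishes at s0 = ρ·s1.
- **The SPIN threshold makes the loss worse by lowering ρ.** Under a linear relation, selection on the pretest lowers ρ but leaves the slope and residual variance alone while it shrinks s0. Start from equal unit SDs and ρ = 0.5, and truncate the pretest at its mean, so that s0² = 0.363. Then ρ falls to 0.33, but the ratio is 0.75/(0.75 + 0.363 × 0.25) = 0.75/0.841 = 0.89. Putting ρ = 0.33 into (1 + ρ)/2 would wrongly give 0.66.
- **About 10 per arm in each cohort makes imbalance likely.** The cohorts are pooled to 110 per arm. The chance pretest difference then has an SE of √(2/110) = 0.135 SD, and allocation within small cohorts does not enlarge it.

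**Conclusion.** The point holds as an avoidable loss of precision. The article fixes the pretest as a level of time and lists other covariates, so this is a stated choice and not a detail left to another document.

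For the pairwise posttest contrast, the change-score variance exceeds the adjusted one by 11% to 54% for ρ from 0.8 to 0.3 with equal SDs. At ρ = 0.5 the excess falls from 33% to about 12% if the pretest SD is 0.8 of the posttest SD. The figures for the omnibus test rest on compound symmetry and an effect confined to the posttest. A reader might infer that the sample size is inadequate or that the planned results would be invalid. Neither follows: 139 and 330 stand as they are.

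**What to change.** In Data Analysis, replace the unadjusted role of the pretest by one of two models, for each outcome:

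1. Model the posttest and follow-up scores with the same outcome's pretest score as a covariate, together with its interaction with time.
2. Keep all four occasions in a longitudinal model that gives the three arms a common pretest mean.

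Either way, keep condition, time, their interaction and the other covariates. Under the first option, state that the treatment effect is the arm difference at the later occasions (condition together with condition-by-time). The interaction alone would then test only whether that difference changes over follow-up.

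The cost is a change of analysis wording, using data already collected in all arms. The named test changes in form but still addresses the treatment effect over time, and the sample size need not be recalculated. The choice should be fixed before the arms are compared.

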## Results

The Ease Online program was developed between July 2019 and December 2020 and officially launched in a press conference on January 18, 2021. The principal investigator and project staff have since been involved in promoting the program and recruiting, screening, and referring participants, taking part in intake interviews and case meetings, conducting service delivery and monitoring duties, collecting data, modifying and enhancing the system, providing technical support, responding to enquiries, and other tasks. As of February 2023, a total of 1811 individuals were enrolled in the Ease Online program. A total of 401 intake interviews have been completed, and 329 participants have joined the program, among whom 166 have completed the intervention. A total of 1924 written comments have been provided for client assignments, 604 individual counseling sessions have taken place, and 392 VRET sessions have been conducted. Data collection is still ongoing, which is expected to be completed in March 2024.

## Discussion

### Overview

SAD often has a high prevalence and low treatment rate. People with SAD often underperform and underachieve. Treatment of SAD can not only improve their achievement and quality of life, but also increase productivity in the society as a whole. This study is the first of its kind in combining iCBT and VRET for the treatment of social anxiety in Hong Kong. At a theoretical level, this study will contribute to the development and evaluation of internet-based psychological interventions in Chinese communities. At a practical level, if proven to be effective, this study will provide an alternative e–mental health service option for people in Hong Kong with easy access. In addition, if adopted by local social service sectors, the Ease Online program will fill in a large service gap between the overwhelming service demand by mental health clients and the insufficiency of mental health professionals in Hong Kong.

### Lessons Learnt

In the process of developing the Ease Online program, several lessons have been learnt: (1) considering the extremely low treatment rate of SAD in Hong Kong (8.7%) [5], iCBT serves as a more preferred and accessible treatment option for Hong Kong clients with SAD; flexibility in time and space as well as the web-based format might encourage people with SAD to seek treatment in a way that is less threatening to them. (2) Culturally relevant intervention contents are important. All of the case demonstration videos were tailored for Hong Kong clients with SAD based on local cases, which increases their relevance and resonates with the real-life situations of the clients. The program focuses on working with culturally relevant beliefs related to social anxiety by choosing CBT skills that have been suitable for Chinese clients in previous studies; for example, the “pie chart” technique is used to relax the cognitive rule of “I have to make no mistakes to be a good offspring.” (3) Compared with cartoons or 3D characters, the use of real humans in VR videos may increase the sense of reality and presence in VR situations. (4) Guided self-help iCBT in service delivery, including therapist support in the form of exercise feedback and counseling sessions, is important to help clients to apply the CBT skills learned from the web-based modules to deal with their social anxiety. (5) Compared to text-based iCBT, Hong Kong people prefer video-based iCBT. As Hong Kong people are generally very busy, they may not have time to read long passages of text. Watching short videos that present the key CBT skills with case demonstration is more acceptable to Hong Kong clients. (6) Participant screening using a screening questionnaire and through intake interviews and case meetings ensures eligibility and screening out of high-risk cases and referring other resources to them. (7) Both the web-based platform and the mobile app are developed as computers and smartphones are widely used in Hong Kong. (8) Aside from psychological assessment, the use of physiological assessments, such as heart rate and blood oxygen levels, in VRET can provide more objective evaluations.

### Limitations

There are several limitations of this study that should be considered. First, only completed tasks are recorded in the system, but there are no records of therapist time and use time of the client in the system. User time can be recorded in the system in future research to calculate the average therapist time spent and the amount of time for which the clients use the system. Second, the number of missing data at posttest and follow-up is quite high—this may be related to the busy lifestyle in Hong Kong and nature of free services provided in this study, although various means including email and phone calls have been used to remind clients to complete the web-based questionnaires after the intervention. Different approaches need to be used in future research to increase the response rate of postintervention assessments. Third, although several strategies are adopted ensuring compliance with the intervention, future research may include independent ratings by certified cognitive behavioral therapists of a random selection of the progress reports of the individual counseling and VRET sessions as well as assignment feedback. Fourth, participants are mainly recruited via open recruitment, which may cause recruitment difficulties and a high nonresponse rate after enrollment. Collaboration with local social service sectors is suggested in future research for participant recruitment and follow-up with service delivery and data collection. Fifth, in the VR system, 180° videos are produced, which may limit the view of clients in the VR environment. Future research may aim to develop 360° videos for the VRET system. Finally, 5 VR scenarios are developed in this study; future research may aim to develop more VR scenarios to allow clients to choose social situations that are more relevant to them.

## Abbreviations

BDI-II: Beck Depression Inventory-II
C-BAI: Chinese version of the Beck Anxiety Inventory
CBT: cognitive behavioral therapy
Ease Online: Ease Anxiety in Social Event Online
iCBT: internet-based cognitive behavioral therapy
RCT: randomized controlled trial
SAD: social anxiety disorder
SPIN: Social Phobia Inventory
VR: virtual reality
VRET: virtual reality exposure therapy
WLC: waitlist control
